### Methods

#### Study Design

A pragmatic exploratory matched-pair cluster randomised study with a nested qualitative semi-structured interview and focus group project. Practices from the Trent and Peninsula research networks will be invited to participate in the study. Researchers at both sites will visit interested practices to explain the research project. Twelve pairs of eligible practices, who agree to participate, will be recruited (6 pairs from South West England and 6 pairs in the East Midlands). The practices will be paired according to level of deprivation (as per Indices of Multiple Deprivation (IMD) quintiles), and ethnicity (as per more or less than 10% non-White population) in their specific electoral wards. One of each pair will be randomly assigned to the standard CVD risk assessment procedure, whilst the other practice within the pair, in addition to providing a standard CVD risk assessment, will also take account of premature CHD familial risk using the family history questionnaire (FHQ). Randomisation will be stratified by study centre. The matched-paired allocation scheme is demonstrated in figure 1. The randomisation list will be prepared centrally by an independent data manager at the University of Nottingham Clinical Trials Support Unit (CTSU). The random allocation sequence will be generated by a computer programme and the treatment allocation for each practice will be obtained by a password-protected internet link. The practices, research staff and participants will not be blinded to group assignment but the study statistician will be. For the statistical analysis treatment arms will be distinguished by a code assigned by the independent data manager at the CTSU. The meaning of these codes will not be revealed to any members of the research team until data analysis is complete. Figure 1 indicates the matched-pair allocation scheme used in this study.

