##### Exclusion criteria

▪ Patients noted to have a previous history of atherosclerotic disease (this includes CHD, CVA & Peripheral Vascular Disease)

▪ Previous history of Diabetes Mellitus

▪ Patients already on statin therapy or other lipid lowering medications

▪ Patients considered by the General Practitioners to be inappropriate to recruit due to psychosocial and other reasons.

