#### Recruitment

Patients, who are offered CVD risk assessment and referred for a cholesterol test as part of their normal care (either at their doctor's initiative or at their own request), will be invited to participate. These patients will be recruited opportunistically, as they present to the GP and practice nurse for a CVD risk assessment. They will be given a study pack, which includes consent forms, participant information sheet, collection of information on CHD risk factors (age, gender, ethnicity) and baseline outcome measures. Participants in the FHQ group will be given, in addition, the Family History Questionnaire. The completed baseline questionnaires and consent forms will be sent to the research team or handed to the practice receptionist, who will forward them to the research team.

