#### Sample size

The sample size for the primary outcome measure is based on the comparison of the change in the percentage of participants classified as being at high CVD risk between treatment groups. The calculation assumes that the proportion of participants at high risk will increase by 3% in the FHQ group and that there will be no increase in the standard risk assessment (control) group. Assuming a power of 80% and a two-tailed alpha of 0.05, 265 participants per group are required to detect a difference of 3%. To allow for the cluster design, an ICC of 0.01 and a cluster size of 40 are assumed. This gives a sample size of 369 participants per group completing CVD risk assessment (i.e. 10 practices per group). This is a conservative estimate since the increase in precision due to the matching of practices is not allowed for as it was difficult to find an estimate of the ICC from matched-pair data.

Further, up to 40 individuals fulfilling the "high risk" criteria, either incorporating or not incorporating family history, will be invited for qualitative interviews (this will be sufficient to reach thematic saturation in major subgroups). Focus groups will be conducted with clinicians at six practices in the FHx arm (approximately 35 individuals in total), which is also estimated to be sufficient for thematic saturation.

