#### Data analysis

Quantitative data: Analysis will be undertaken on an intention to treat basis in that participants will be analysed in the groups to which they were allocated. The primary time point of interest is 6 months. Practices will be included in the analysis provided complete data (the outcome of interest at baseline and at 6 months follow up, and participant/practice level data that will be adjusted for in the analysis) are available for at least one of the participants recruited to the practice. Participants within the practice with incomplete data will be excluded from the analysis. If data for the secondary outcomes are missing for the 6 month assessment, a sensitivity analysis will be performed in which data from the two week assessment will be carried forward. An analysis assuming the worst case scenario of the 6 month assessment value being the same as the baseline value will also be performed.

The distribution of participants in average, moderate and high risk categories will be described by treatment group. The increase in the proportion of participants at high risk of CVD in the next 10 years as a result of incorporating systematically collected family history into CVD risk assessment score will be presented. For the primary outcome measure and the secondary outcome measures that are binary variables, the statistical significance of the difference in the event rates (e.g. the mean proportion of participants at high risk) between the FHQ and control groups will be calculated using a weighted paired t-test after the adjustment for the pairing of practices, participant and practice level variables that are associated with the outcome of interest. A weighted paired t-test will be used because it is anticipated that there will be wide variation in the number of participants recruited per practice. The robustness of the t-test will be assessed using a permutation test. Continuous outcome variables will be analysed using a similar method with differences in the mean response between the FHQ and control groups being compared using a weighted paired t-test. 95% confidence intervals will be presented for the intervention effect for all outcome measures.

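### The primary analysis does not secure adjustment for the family-history-free JBS2 result, although recruiters probably know their arm and the sample size assumes that this result is netted out

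*Protocol article*

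**What the plan says.** The Data analysis section of Phase 2 tests the difference in the proportion at high risk between the FHQ and control groups. It uses a weighted paired t-test, checked by a permutation test, after "adjustment for the pairing of practices, participant and practice level variables that are associated with the outcome of interest". It names no covariate.

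The Sample size section is built on a different quantity, the change in the percentage at high risk. It assumes that "the proportion of participants at high risk will increase by 3% in the FHQ group and that there will be no increase" in controls. With 80% power and two-sided 5% significance this gives 265 per group. For clustering, "an ICC of 0.01 and a cluster size of 40 are assumed", and the result is 369 per group.

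On recruitment, Study Design states: "The practices, research staff and participants will not be blinded to group assignment". The Recruitment section adds: "These patients will be recruited opportunistically, as they present to the GP and practice nurse for a CVD risk assessment". Only packs in the FHQ arm contain the Family History Questionnaire. The exclusion criteria leave room for judgement: "Patients considered by the General Practitioners to be inappropriate to recruit due to psychosocial and other reasons".

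Data collection procedures has the research team calculate JBS2 scores for all participants, with familial risk then added in the FHQ arm only. A result without family history is therefore obtainable in both arms.

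**The concern.** Randomising practices balances practices on average. It does not balance the patients whom those practices go on to recruit. An arm-specific pack means that the recruiting GP or nurse very probably knows the allocation, although the article does not state the order of allocation and recruitment in one sentence. If the two arms recruit people of different standard risk, the difference appears in the primary outcome as if family history had caused it.

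The standard JBS2 result is the variable that deals with this. In controls it fixes the primary outcome completely, because nothing is added to it. In the FHQ arm it decides the outcome for most participants. A rule that asks only for association with the outcome does not guarantee that this variable enters, or in what form. At stake are the power that the sample size promises and protection against a recruitment difference as large as the effect sought.

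**Working it through.** **Inputs from the protocol article.** Effect: +3% against 0%; two-sided alpha 0.05; power 80%; ICC 0.01; cluster size 40; 265 and 369 per group (Phase 2 Sample size). At least 5% at high risk (Phase 1 Sample Size). Twelve pairs (Study Design). 400 per arm expected (Attrition rate).

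**The plan's own figure.**
- Design effect: 1 + 39 × 0.01 = 1.39.
- 265 × 1.39 = 368.35, rounded up to 369. Reproduced.
- The two-proportion formula for 0% against 3% gives 257, and 257 × 1.39 = 357.23, so 358, within 3% of 369.
- At 265 per group, power is 81.3% by normal approximation and 80.8% by Fisher's exact test. The 265 is acceptable for 0% against 3%.

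**The same trial if proportions are compared without the standard result.** Take 5% in controls and 8% in the FHQ arm.
- Required before clustering: 1,059 per arm.
- After clustering: 1,059 × 1.39 = 1,472.01, so 1,473 per arm.
- Power with 369 per arm (effective 369/1.39 = 265): about 29%.
- Power with 400 per arm (effective 400/1.39 = 288): about 31%.

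**Standard errors at the expected recruitment.** 400/12 = 33.3 per practice, so the design effect is 1 + 32.3 × 0.01 = 1.323 and the effective number is 400/1.323 = 302 per arm.
- Raw 5% v 8%: √((0.0475 + 0.0736)/302) = 0.0200, or 2.0 points.
- Chance difference between arms in standard-score high risk: √(2 × 0.05 × 0.95/302) = 0.0177, or 1.8 points; 95% range ±3.5 points.
- Reclassification alone: √(0.03 × 0.97/302) = 0.0098, or 1.0 point.

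**Simulation** (12 pairs, 33 per practice, ICC 0.01, equal-weight paired t-test, 20,000 runs, true effect 3 points):

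| Standard-score high risk | Raw: SE, power | Net of standard result: SE, power |
|---|---|---|
| 5% | 1.9 points, 29% | 0.9 points, 97% |
| 10% (assumption) | 2.6 points, 20% | 0.9 points, 96% |

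**Recruitment difference, true effect zero.** The article gives no size, so 1 to 3 points more standard-score high risk in the FHQ arm is an assumed range.

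| Assumed excess | Bias of raw estimate | Rejections at 5% (5% baseline) | Rejections at 5% (10% baseline) |
|---|---|---|---|
| 1 point | 1 point | 8% | 7% |
| 2 points | 2 points | 16% | 11% |
| 3 points | 3 points | 27% | 18% |

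The estimate net of the standard result stays at zero throughout. With a true effect of 3 points, the 5% baseline and an excess of +2 or −2 points, the raw estimate is 4.9 or 1.1; the net estimate is 2.9 or 3.1.

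**Dependence on model form.** With an assumed skewed score distribution, 5% at or above 20%, and 12 pairs of 33, the raw SE is again about 1.9. A linear term in the score lowers it only to about 1.3. Adding the three risk categories, or using a logistic first stage, lowers it to about 0.95 to 1.0.

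**The case against.** **The covariate list may sit elsewhere.** This stands in part. An article may leave the list to a fuller document, and its absence is not the point here. The point is that the rule the article does state fails to secure the one variable that matters, and an analysis plan written to that rule would inherit the gap.

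**The rule would pick up the standard score anyway.** Nothing forbids it. The sample size speaks of change, and the analysis section requires the outcome at baseline for inclusion, so the design points that way. Neither statement makes it an adjustment variable for the primary test or fixes its form, and the form decides much of the gain.

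**The reclassification is presented in any case.** The plan does promise to report the increase due to incorporating family history, and that report separates the two components. It is descriptive and is not the primary comparison.

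**Selection on standard risk is limited.** Cholesterol results arrive after recruitment, candidates are already referred for a test in usual care, and pairs are matched on deprivation and ethnicity. All true; this bears on the likely size of the bias, which is unknown. It does not affect the loss of power.

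**Stronger readings that the article does not support.** A reader might infer that covariates will be picked from associations observed in the trial data, so that p-values are unreliable. The text does not say that the association is tested in the trial data; prior knowledge is an equally possible reading. The statistician is blinded to the arm codes, and a permutation test is planned, which stays valid if the selection ignores arm. Nor may the chance imbalance of 1.8 points be read as bias: a valid paired t-test already reflects it. It is a matter of precision.

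**Conclusion.** The point holds as one of power and protection. The primary test as described is not tied to the quantity behind the 369 per group. Left without the standard JBS2 result, it has a standard error of about 1.9 to 2.0 points and roughly 30% power at a 5% baseline, less if the baseline is higher, and it passes any recruitment difference in standard risk straight into the estimate.

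The reduction to about 1.0 point, with power near 97%, is idealised. It assumes zero change in controls, which is true by construction when the change is taken from the same score, and it depends on model form. The size of any recruitment difference is an assumption.

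Adjustment removes only differences in standard risk. If unblinded FHQ practices preferentially recruit people with a family history, a family-history-free score cannot correct for that.

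**What to change.** In the Data analysis section, pre-specify that the primary comparison is adjusted for, or taken as the change from, each participant's standard family-history-free JBS2 result. State the form so that the 20% threshold is respected. Two options are a first-stage regression on the score plus its three categories (below 10%, 10 to 19%, 20% or more), or a logistic first stage on the score. Either should omit arm. Practice-level residuals then go into the planned weighted paired t-test and permutation test.

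For each secondary outcome, pre-specify its baseline value as the covariate. Confine covariates chosen by association to sensitivity analyses.

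Add one sentence saying that this does not correct differential recruitment by family history.

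The cost is wording only. The scores are already to be calculated for everyone and checked by a second team member. The sample size does not change.

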#### Ethical considerations

We do not foresee major ethical issues arising from our study. Filling the FHQ may transiently raise patients' anxiety[21], but we are recruiting patients who have either requested CVD risk assessment themselves or been offered it by their doctor, so we are not increasing anxiety in a previously unaware population. We will follow normal ethical procedures to ensure informed consent, confidentiality and data protection.

## PHASE 3: THE FEASIBILITY OF INCORPORATING CHD FAMILY HISTORY INTO CHD RISK ASSESSMENT IN PRIMARY CARE: AN ECONOMIC PERSPECTIVE

### Overview

The resources available to provide health care are limited and therefore, it is important to establish if incorporating the systematic family history tool into CVD risk assessments is both effective and cost effective, that is, does the family history tool offer value for money. This phase will establish the costs of the intervention and the cost consequences of using the family history tool alongside estimating the benefits of using the tool. Using data from phases 1 and 2, (and if necessary other published data), an economic evaluation of the systematic incorporation of family history into CVD risk assessment compared to current practice from an NHS primary care perspective will be undertaken over the trial period. Established and accepted economic methodologies will be employed throughout[39]. This phase will achieve outcome 5 of the study.

### Methods

A cost analysis will be undertaken. Resource items likely to change as a result of the intervention (as well as the cost of developing and providing the intervention) will be identified and measured (collected using MIQUEST software) during phase 1 and 2. Unit costs will be derived from national published data[40,41] and used to value the resources measured for a common price year.

If the family history tool is to improve outcomes it not only needs to identify more at-risk individuals at an earlier stage (although this is likely to induce some benefit compared to usual practice in and of itself) but also lead to behavioural change. Such behavioural change is likely to take time as people go through stages of change towards permanent change. Therefore, the six month period of the trial may only be sufficient to detect the change in numbers identified rather than any actual change to health-related quality of life brought about through behavioural change. To test if this is in fact the case, two outcomes will be measured and two approaches to economic evaluation employed. This study will estimate the cost-effectiveness in terms of cost per additional high risk individual identified and the cost utility using the SF-6D administered at baseline and 6 months[35] to estimate the cost per QALY over the trial period (with use of 2 week score for sensitivity analysis, if 6 month score not available). Both analyses enable technical efficiency questions to be addressed, that is how best to identify those at high risk of CHD (applying a systematic approach to family history collection or not) whilst the cost-utility analysis will also enable allocative efficiency questions to be addressed, that is whether resources spent on using a systematic approach to CHD family history collection are considered cost-effective compared to a diverse range of other health interventions or services.

The timeframe for the economic analysis will be that of the trial period. If non-dominance occurs (that is if costs are greater and the intervention is more effective or if the intervention is cheaper and less effective) an incremental cost-effectiveness ratio (the ratio of change in cost divided by change in benefit comparing the systematic approach to family history collection versus usual care) will be produced. The confidence region around the incremental cost effectiveness ratio will be estimated and presented using appropriate statistical techniques[42]. Appropriate sensitivity analyses will be undertaken to test the robustness of the results.

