#### Data collection procedures

After initial recruitment, all participants will have their medical records reviewed to reconfirm their eligibility. On arrival of the cholesterol blood results, CVD risk scores will be calculated by the research team, as per JBS2 guidelines[1]. In the FHQ group, familial CHD risk will also be calculated and incorporated into the overall score. Two weeks after the original consultation both clinicians and participants will be sent a letter informing them about the participant's risk status. Participants identified at average or moderate CVD risk in both groups will be sent a letter confirming status together with a leaflet on lifestyle advice. In addition to a leaflet, those at higher risk in both groups will be informed that they are at higher than average CVD risk and invited for a consultation in the practice within the next 2 weeks.

In the consultation with doctor or nurse, participants will have their CVD risk explained and given lifestyle advice and, when clinically indicated, statins will be offered, as per usual practice. Participants in the FHQ group will also have the impact of premature CHD family history on the CVD risk score explained.

At two weeks and six months after the second consultation (for high risk participants) or letter being sent (for average or moderate risk participants) all participants will be posted a set of questionnaires. Participants, who have been identified at high risk, will be invited for a qualitative interview by phone, following a purposeful, maximum variation sampling strategy in terms of being in intervention or control arm, gender, age, occupational class, ethnicity, region and having or not having a family history of premature CHD. Recruitment will continue until thematic saturation is reached. Participants in the qualitative study will be interviewed by an experienced researcher in their homes (or if the participants so desire by phone) at 2 weeks and 6 months after the consultation in the practice.

Six practices in the intervention arm will be invited to participate in a focus group to capture the practitioners' views on using family history assessment and incorporate this into their clinical decision making.

After nine months the recruited participants' computer GP records will be reviewed for prescribing of: lipid lowering, anti-obesity, and anti-thrombolytic drugs, as well as nicotine replacement therapy.

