#### Attrition rate

One thousand four hundred patients will be invited to participate. It is estimated that one thousand participants will complete consent and baseline questionnaire, with eight hundred completing the CVD risk assessment by having the serum cholesterol test, resulting in 400 participants recruited in each arm of the study.

Further, related to secondary outcome measures, it is estimated that 60% of recruited participants will complete the 6 month questionnaire. Hence 300 participants in each arm are expected to complete the study.

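### The main cost-per-QALY analysis gives no weight to the 2-week SF-6D, although the score appears to be collected and would carry half the weight in a trapezium-rule QALY

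*Protocol article*

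**What the plan says.** The Methods of Phase 3 define the cost-utility analysis as "the cost utility using the SF-6D administered at baseline and 6 months", and add a fallback: "with use of 2 week score for sensitivity analysis, if 6 month score not available". The time points of the main QALY are therefore a stated choice, not a detail left open.

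Other sections indicate that a 2-week SF-6D will exist. Under Data collection procedures in Phase 2, at two weeks and again at six months "all participants will be posted a set of questionnaires". Outcome measures lists the SF-6D among the secondary outcomes, and the fallback itself refers to a 2-week score. No section says outright that the 2-week pack contains the SF-6D, so this is an inference, though a strong one.

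The clock for these questionnaires does not start at baseline. Baseline measures come with the study pack at recruitment ("collection of information on CHD risk factors (age, gender, ethnicity) and baseline outcome measures"). Then: "Two weeks after the original consultation both clinicians and participants will be sent a letter informing them about the participant's risk status". Participants at higher risk are in addition "invited for a consultation in the practice within the next 2 weeks". The follow-up questionnaires are timed from the letter (average or moderate risk) or from the second consultation (high risk).

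**The concern.** A QALY is utility accumulated over time. With two measurements, the usual calculation draws a straight line from baseline to 6 months. Half the result then comes from a score taken before anyone knew their risk, and whatever was measured in between has no influence. Any difference between arms that appears soon after the risk is communicated is reduced if it lasts and lost altogether if it has gone by 6 months.

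The QALY difference is the denominator of the incremental cost-effectiveness ratio and helps decide whether one strategy dominates. If the 2-week and 6-month differences have opposite signs, the two- and three-point versions can even disagree on the direction of the QALY difference.

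A smaller issue is the fallback. Putting the 2-week score in place of a missing 6-month score assumes no change between the two, whereas the same section argues that behavioural change takes time.

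**Working it through.** The protocol gives no QALY figure, weight or formula, so there is nothing to reproduce. The area under the curve by the trapezium rule is assumed.

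**Timings** (from Data collection procedures, taking 6 months as 26 weeks and baseline as the original consultation):
- Letter at week 2: scores at weeks 0, 2 + 2 = 4, and 2 + 26 = 28.
- Second consultation at the latest invited time, week 4: scores at weeks 0, 4 + 2 = 6, and 4 + 26 = 30.

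**Weights.** For times t0 < t1 < t2 and T = t2 - t0, the shares of the area are (t1 - t0)/2T for baseline, (t2 - t0)/2T = 1/2 for the middle score, and (t2 - t1)/2T for the last score. The middle share is one half whatever its timing. With two points the shares are 1/2 and 1/2.

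| Schedule | Baseline | 2-week | 6-month |
|---|---|---|---|
| Weeks 0, 4, 28 | 4/56 = 0.071 | 0.500 | 24/56 = 0.429 |
| Weeks 0, 6, 30 | 6/60 = 0.100 | 0.500 | 24/60 = 0.400 |
| As planned, two points | 0.500 | 0 | 0.500 |

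**Effect on the QALY difference.** The difference is (share × SF-6D difference, summed over scores) × T/52. The protocol has no SF-6D values, so a between-arm difference of 0.02 is assumed for illustration. The ratios between methods do not depend on it.

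| Pattern of the difference | Two points, 0/28 | Three points, 0/4/28 | Two points, 0/30 | Three points, 0/6/30 |
|---|---|---|---|---|
| 0.02 at both follow-ups | 0.0054 | 0.0100 | 0.0058 | 0.0104 |
| 0.02 at 2 weeks only | 0 | 0.0054 | 0 | 0.0058 |
| 0.02 at 6 months only | 0.0054 | 0.0046 | 0.0058 | 0.0046 |
| Straight-line growth to 0.02 at 6 months | 0.0054 | 0.0054 | 0.0058 | 0.0058 |

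- Both follow-ups: ratio (0.500 + 0.429)/0.500 = 1.86, or (0.500 + 0.400)/0.500 = 1.80. With the cost difference unchanged, the cost per QALY differs by the same factor.
- 6 months only: ratio 0.429/0.500 = 0.86, or 0.400/0.500 = 0.80, so the three-point value is 14% or 20% lower.
- Straight-line growth: the 2-week difference would be 0.02 × 4/28 = 0.0029 or 0.02 × 6/30 = 0.0040, and the two methods agree.

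**Reach of the fallback.** Attrition rate expects that "60% of recruited participants will complete the 6 month questionnaire", which leaves 40% without a 6-month score. The same section expects 300 completers per arm out of 400 recruited, which would leave 100/400 = 25%. Either way, the substitution is confined to a sensitivity analysis.

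**The case against.** The strongest objection is that three points can do worse than two. Suppose SF-6D falls by 0.02 by week 4 and has recovered in a straight line by week 8. The true loss is 0.5 × 0.02 × 8/52 = 0.0015. Three points at weeks 0, 4 and 28 record 0.0054, an error of 0.0038; two points record zero, an error of 0.0015. Under this shape, two points are closer whenever recovery is complete before week 14 (half of 28), or week 15 on the later schedule. This stands, and it is the reason to keep the two-point result. It does not justify ignoring a measured utility in the main analysis, because a lasting early change is then always understated.

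A second objection is that the authors doubt that six months will show any quality-of-life change from altered behaviour. That also stands: the factor of 1.8 to 1.9 belongs to one pattern and is not a forecast. If the effect builds steadily, the choice makes no difference.

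Two stronger readings are tempting, but the protocol does not support them:
- A reader might take Ethical considerations to predict an early utility loss in the intervention arm. It says only "Filling the FHQ may transiently raise patients' anxiety". Anxiety is measured separately with the STAI, the FHQ is handed out at recruitment, and the 2-week questionnaire follows some 4 to 6 weeks later.
- A reader might infer that up to 40% of participants have a substituted score in the main cost per QALY. The protocol limits the substitution to a sensitivity analysis.

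Finally, the article promises appropriate sensitivity analyses. These could include a three-point QALY, but nothing commits to one.

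**Conclusion.** The point holds as a fault in a stated analysis choice. The main QALY gives zero weight to a score that would carry half of it, and raises the pre-intervention share from 7-10% to 50%. A difference present at both follow-ups would be understated by a factor of 1.8 to 1.9, and one present only at 2 weeks would be missed entirely. A difference seen only at 6 months would move by 14-20% in the other direction, and a steadily growing one not at all.

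This rests on three assumptions: QALYs are computed as area under the curve, the 2-week pack contains the SF-6D, and questionnaires arrive near their scheduled times. The direction and size of any actual bias cannot be known from the protocol. The point concerns the cost-utility part of Outcome 5 in an exploratory study and leaves the primary outcome untouched. It is worth correcting because the remedy is cheap.

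**What to change.** - State that the main QALY is calculated from the SF-6D at baseline, 2 weeks and 6 months by the trapezium rule, using each participant's actual questionnaire dates, with the between-arm comparison adjusted for baseline SF-6D.
- State explicitly that the SF-6D is part of the 2-week questionnaire.
- Keep the baseline-and-6-month QALY as a named sensitivity analysis, because straight-line interpolation overstates an early change that resolves quickly.
- In the sensitivity analysis for missing 6-month scores, use the 2-week score as a predictor in multiple imputation instead of substituting it.

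The cost is a little more analysis and the imputation of some missing 2-week scores. If the 2-week pack contains the SF-6D, no additional data collection is needed.
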